## 2. Problem Statement and Justification

Patients under mechanical ventilation (MV) in the intensive care unit (ICU) exhibit high hospital mortality rates, ranging from 23% to 51%. This mortality is linked to the success of weaning and the incidence of nosocomial infections. Prolonged MV can increase complications in critically ill patients, extending immobility and raising the risk of ventilator-associated pneumonia, further restricting patients. It is argued that early mobility improves MV-related outcomes, such as ventilator duration and ventilator-free days, breaking the vicious cycle of prolonged MV and immobilization. Additionally, early rehabilitation is associated with reduced morbidity and mortality, as well as complications of the disease, ICU length of stay, hospital stay, and rehospitalization rate. Therefore, weaning from MV through early rehabilitation is crucial to improving the prognosis of ICU patients.

Despite the growing evidence on the utility of early rehabilitation for critically ill patients, programs and interest in outcomes vary among studies. Given this diversity, healthcare professionals must assess whether different programs have a similar therapeutic effect and ensure that the prescribed rehabilitation provides benefits consistent with previous literature. Besides the heterogeneity among programs, different countries and institutions face barriers to implementation, such as a shortage of trained rehabilitation personnel and a cultural gap in the ICU. In cases of personnel

shortages and settings with conservative ICU ethics, early rehabilitation is adapted to a sustainable level, including modified programs or less frequent visits.

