### 6.8 Losses and Handling of Missing data

- Frequency and Distribution: Losses during follow-up were recorded for participants in both study groups. Of [total number of participants] initially assigned, [number of participants lost] were lost during the study period.
- Reasons for Losses:
  - o Voluntary withdrawal of consent by the participant.
  - o Adverse events not related to the study treatment.
  - o Failure to comply with the study protocol.
  - o Transfer to other medical facilities.
- Comparison between Groups: A comparative analysis will be carried out between the control and intervention groups, to assess the equitable distribution of losses.
- Characteristics of Lost Participants: The baseline demographic and clinical characteristics of participants who completed the study will be compared with those who were lost to follow, to assess whether the losses introduced substantial biases.

- **Impact on Analysis:** A sensitivity analysis will be performed to evaluate the potential impact of losses on the study results. Results will be presented with both the inclusion and exclusion of missing participants.

- **Statistical Management:** In the main statistical analysis, the intention-to-treat approach will be used, including all participants according to their original assignment, regardless of their compliance or loss to follow-up. We will also perform a sensitivity analysis based on a per-protocol analysis since it could provide us with a measure of the effect of weaning under ideal treatment adherence conditions.

- **Replacement of Lost Participants:**

- o **Ethical Consideration:** Before considering the replacement of lost participants, an ethical evaluation of the justification for such action will be conducted. It will be considered whether the replacement is ethically acceptable and whether its implementation respects the rights and well-being of the participants.

- o **Imputation Methods:** If replacement of lost participants is considered, statistically sound and well-founded imputation methods will be used. Options such as imputation by the mean, LOCF, or other more advanced methods such as multiple imputation will be explored.

- o **Transparency and Documentation:** A detailed description of the imputation methods used will be provided, including the reasons for choosing a specific method. This will be included in the final reports and communication with the Ethics Committee.

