| Days from the start of ventilatory support to the start of weaning | Days from the start of ventilatory support (intubation) to the start of weaning                                                                                                                   | Discrete Quantitative   | Days                                                                                                                                                                                                     |
| Days of mechanical ventilation                                     | Days of invasive mechanical ventilation                                                                                                                                                           | Discrete Quantitative   | Days                                                                                                                                                                                                     |
| Days free of mechanical ventilation                                | 28 days minus ventilation days                                                                                                                                                                    | Discrete Quantitative   | Days

It will be defined as 0 if the patient dies or has been ventilated for more than 28 days.                                                                                                    |
| Delirium                                                           | For a patient to be considered to have delirium according to the CAM-ICU, both the first criterion (acute alteration in mental status) and at least one of the other three criteria (inability to | Qualitative Nominal     | 
 
1. Acute alteration of mental status (+/-).
 
2. Inability to maintain sustained attention (+/-).
 
3. Disorganization of thought (+/-).
 
 |

|                                          |                                                                                                                                |                       |                                                        |
|------------------------------------------|--------------------------------------------------------------------------------------------------------------------------------|-----------------------|--------------------------------------------------------|

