|                                          | maintain sustained attention, disorganization of thought, or fluctuating changes in level of consciousness).                   |                       | 4. Fluctuating changes in level of consciousness (+/-) |
| Days of delirium                         | Days with the presence of delirium                                                                                             | Discrete Quantitative | Days                                                   |
| Sedation days                            | Days with sedation                                                                                                             | Discrete Quantitative | Days                                                   |
| Sedation-free days                       | 28 days fewer days of sedation                                                                                                 | Discrete Quantitative | Days
It will be defined as 0 if the patient dies.   |
| Barthel index at hospital discharge      | The Barthel Index is a scale used to measure a person's degree of functional independence in activities of daily living (ADL). | Discrete Quantitative | It will be 0 if the patient dies.                      |
| Days of hospital stay                    | Days of hospital stay                                                                                                          | Discrete Quantitative | Days                                                   |
| Days of ICU stay                         | Days of ICU stay                                                                                                               | Discrete Quantitative | Days                                                   |
| Mortality                                | Death                                                                                                                          | Qualitative Nominal   | Yes or no                                              |
| Time from intubation to start of therapy | Time from intubation to start of therapy                                                                                       | Discrete Quantitative | Days                                                   |

Association between early multimodal therapy and days of mechanical ventilation in the intensive care unit of the Fundación Santa Fe de Bogotá: A randomized controlled clinical trial.

Version 6.0

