| Grip strength at the time of extubation | Grip strength of the dominant hand within 24 hours after extubation                                                                                   | Continuous Quantitative | Kilograms

It will be 0 if the patient dies. |
| Failed extubation                       | Inability to breathe spontaneously in the first 48 hours after removal of the artificial airway and the patient is unable to maintain a patent airway | Qualitative Nominal     | Yes or no                                          |
| NIV POS extubation                      | Post-extubation non-invasive ventilatory support within 48 hours                                                                                      | Qualitative Nominal     | NOT = 0

IF = 1                              |
| Prolonged mechanical ventilation        | Invasive mechanical ventilation longer than 14 days                                                                                                   | Qualitative Nominal     | Yes or no                                          |
| Tracheostomy                            | Need to use a tracheostomy tube.                                                                                                                      | Qualitative Nominal     | Yes or no                                          |
| Adult respiratory distress syndrome     | Bilateral alveolar infiltrates with a PAFI less than 300.                                                                                             | Qualitative Nominal     | Yes or no                                          |

|                              |                                                                                                                   |                     |                                                                                                                                                                                                                                                    |
|------------------------------|-------------------------------------------------------------------------------------------------------------------|---------------------|----------------------------------------------------------------------------------------------------------------------------------------------------------------------------------------------------------------------------------------------------|

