Variables that could act as confounding factors will be evaluated through a second multiple regression model. In this model, the potentially confounding variable will be removed, and the resulting slope or estimator (adjusted estimate) will be calculated. If there is a change greater than 15%-20%, the confounding variable will be included in the final model. Otherwise, the most parsimonious model will be chosen.

To evaluate the interaction between two variables, another regression model will be performed, including a new variable resulting from multiplying the two potentially interacting variables. If the regression coefficient of this new variable has a significance level of less than 0.05, it is concluded that there is an interaction, and this variable will be included in the model. Variables with potential interaction will be identified by evaluating confounding factors. Researchers will also evaluate clinical variables that may be considered as interaction or confounding variables through the above-described strategy.

The assumption of proportional hazard will be evaluated using Schoenfeld residuals, and influential values will be analyzed through residuals versus observations plots. Multicollinearity will be assessed through matrix curves.

Logistic regression models will be used to assess the relationship between our dichotomous variables, such as failed extubation, post-extubation NIV, prolonged mechanical ventilation, tracheostomy, and dysphonia, and the other studied variables. The assumptions of a logistic regression model, such as linearity in the log of the odds, independence of errors, homogeneity of variance, absence of multicollinearity, absence of outliers, and proportionality of effects, will be evaluated through residual analysis and graphical diagnostics, such as Pearson residual analysis or deviance residual analysis.

A multiplicity adjustment strategy will be employed in statistical tests, such as the Bonferroni method, Holm-Bonferroni, or other methods that control the false discovery rate (FDR), to maintain the overall type 1 error rate at an acceptable level.

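### Prolonged mechanical ventilation has no rule for death: a patient who dies on the ventilator before day 14 is coded No, the same as a patient extubated alive early

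*Protocol*

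**What the plan says.** In the Protocol's variable table (section 6.11), the whole definition of prolonged mechanical ventilation is "Invasive mechanical ventilation longer than 14 days", with the categories yes and no. The row does not mention death. Section 6.8, section 6.13 and Annexes 4 and 5 add no death rule for this variable.

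Other rows of the same table do have one. For ventilator-free days: "It will be defined as 0 if the patient dies or has been ventilated for more than 28 days". For sedation-free days: "It will be defined as 0 if the patient dies". For the Barthel index, JH-HLM mobility and grip strength: "It will be 0 if the patient dies".

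Section 6.13, repeated in the Summary, applies logistic regression to dichotomous variables "such as failed extubation, post-extubation NIV, prolonged mechanical ventilation, tracheostomy, and dysphonia, and the other studied variables". Section 6.8 says that in the main statistical analysis "the intention-to-treat approach will be used, including all participants according to their original assignment". Prolonged ventilation does not appear among the primary, secondary, exploratory or safety outcomes in section 6.6.

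**The concern.** A yes/no cut on ventilation days cannot tell why ventilation ended. Death and recovery both stop the count, so both give No if they happen before day 14. A patient who dies ventilated on day 6 then has a more favourable code than a survivor extubated on day 16.

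The plan also treats the same death in opposite ways. The day-6 death scores 0 ventilator-free days, the worst value, and No for prolonged ventilation, the code shared with early extubation.

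Death is foreseeable here. Section 2 says ventilated ICU patients "exhibit high hospital mortality rates, ranging from 23% to 51" percent, and section 6.7 lists death in the ICU among the reasons for stopping the intervention. What is at stake is the direction and meaning of a logistic model on this variable: it could show less prolonged ventilation in an arm because more of that arm died early.

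**Working it through.** **Literal coding.** Four records under the section 6.11 definitions:

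| Course | Prolonged ventilation | Ventilator-free days |
|---|---|---|
| Extubated alive, day 5 | No | 28 − 5 = 23 |
| Died ventilated, day 6 | No | 0 (death rule) |
| Extubated alive, day 16 | Yes | 28 − 16 = 12 |
| Still ventilated after day 28 | Yes | 0 |

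The second row is the problem: worst value on one variable, same code as early success on the other.

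**Size.** The plan states no rate for this variable, so there is no figure to reproduce. Let d be the probability of dying on the ventilator before day 14, and q the probability of ventilation beyond day 14 among the rest. Both are assumptions. q is set equal in the two arms, so therapy has no effect on ventilation. The arm size of 37 is from the protocol.

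- Literal rule: P(Yes) = (1 − d) × q
- Death counted as unfavourable: P = d + (1 − d) × q

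The second formula covers deaths on the ventilator only. Deaths after extubation by day 14 would add to it.

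With d = 15% in one arm and 30% in the other:

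| q | Literal, d = 15% | Literal, d = 30% | Odds ratio | Death unfavourable, d = 15% | Death unfavourable, d = 30% | Odds ratio |
|---|---|---|---|---|---|---|
| 15% | 0.85 × 0.15 = 12.8% | 0.70 × 0.15 = 10.5% | 0.80 | 27.8% | 40.5% | 1.77 |
| 25% | 0.85 × 0.25 = 21.3% | 0.70 × 0.25 = 17.5% | 0.79 | 36.3% | 47.5% | 1.59 |

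Odds ratios compare the arm with more deaths to the arm with fewer. In patients, the literal rule gives 4.7 against 3.9 of 37 at q = 15%, and 7.9 against 6.5 of 37 at q = 25%: a shift of about one patient.

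**Wider range.** With q from 10% to 40%:

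- d = 10% against 20%: literal odds ratios 0.84 to 0.88.
- d = 10% against 30%: literal odds ratios 0.69 to 0.76, a shift of about 1 to 3 patients. Counting death as unfavourable gives 1.62 to 2.50, the opposite direction.
- Equal d in both arms (10% each): odds ratio 1.00. No between-arm bias, but the No group still contains both deaths and early recoveries.

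**The case against.** The strongest reply is that this is a factual descriptor and not an endpoint. A patient who died on day 6 was indeed not ventilated for more than 14 days, and the protocol never calls No the good result. The zero for ventilator-free days reflects a variable built to combine death and duration, so it does not oblige every duration variable to rank death last. The logistic paragraph describes broad modelling of factors and names no arm contrast on this variable, and intention to treat is tied to the main analysis, which this is not.

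Much of that stands, and it limits the importance of the point. It does not remove the defect. The plan names the variable for a regression on the other studied variables, and study group is one of the variables in the table. Whichever predictor is used, the model would treat deaths and early extubations as the same result.

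The reply on size also stands. Mortality of 23–51% is general hospital mortality, not death on the ventilator before day 14, and the exclusions (cardiac arrest, life expectancy under 180 days, baseline Barthel below 70) may lower it. The sample-size figure of 6.1 ± 1.4 days in the usual-care group, taken at face value, puts 14 days (14 − 6.1) / 1.4 = 5.6 standard deviations above the mean, so few patients might pass day 14 at all.

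A reader might infer that the trial as a whole would reward the arm with more early deaths. The documents do not support this. Ventilator-free days to day 28, a listed secondary outcome, are 0 at death. All-cause mortality to day 90 is reported separately. Nothing in the protocol predicts unequal early deaths.

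**Conclusion.** The point holds as a coding gap in one named analysis variable. The definition gives death on the ventilator before day 14 the same code as early extubation, and no other text corrects it. That No is the only available code is a consequence of the definition; the protocol does not say so in words.

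A between-arm tilt requires unequal early deaths on the ventilator. On the assumed 15% against 30%, with q of 15–25%, it is about one patient per 37, in favour of the arm with more deaths. That affects direction and interpretation; it is no basis for expecting a false significant result. With equal deaths the variable is still hard to interpret, because it pools failures with successes. The primary outcome, the sample size and the listed secondary outcomes are not affected.

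**What to change.** State in sections 6.11 and 6.13, and in the Summary, how death is handled for this variable. For the logistic model, use dead from any cause by day 14 or ventilated beyond day 14, against alive and extubated by day 14. Say explicitly that death after extubation but by day 14 counts as unfavourable; otherwise a patient extubated on day 4 who dies on day 10 has no clear code. Report three groups separately: alive and extubated by day 14, ventilated beyond day 14, and dead by day 14.

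The change is to wording. Ventilation start and end dates and mortality are on the collection form, and the section 6.11 table has a row that appears to record days to death. The Annex 5 form shows mortality only as yes or no, so check that the time of death is carried into the database. The downside is a composite that mixes death with long ventilation, which the three-group table shows openly.

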### Procedures for Data Collection

Data will be collected by clinical staff, therapists, and research assistants from the intensive care unit, all of whom are familiar with the study and the predefined variables. The interventions and variables collected by the therapists are detailed in the Clinical Trial Operational Plan (Annex 1). Data collection will take place on the third and fourth floors of the Intensive Care Unit at FSFB. Training will be provided to all investigators on data collection and the specific times to complete the data collection instrument. Additionally, knowledge of the protocol will be assessed through an exam, which will be considered passed with a score above 4, and feedback will be provided to address any deficiencies. The variables measured by the therapists will be recorded daily from the start of the intervention. Measurements will be taken at five key points in the research: upon admission, during observation in the intensive care unit, at the start of weaning from ventilatory support, before and after extubation, and at the end of observation. Finally, a follow-up will be conducted 90 days after endotracheal intubation, during which patients or their legal representatives will be contacted by phone to assess mortality.

To ensure data quality, the following strategies will be implemented:

**Data Validation During Entry:** Verification of formats, ranges, and logical consistency of the data will be performed at the time of entry.

**Double Data Entry:** Two investigators will independently enter the same data, and then compare them to identify discrepancies. Any discrepancies found will be investigated and corrected.

**Consistency and Coherence Verification:** Checks will be carried out to ensure that the data do not present contradictory or incoherent information in the records.

**Extreme Value Checking:** Extreme or atypical values in the data will be identified and verified to ensure their validity.

**Quality Control in Later Stages:** Cross-checks will be performed, random samples of the results will be reviewed, and external validation methods will be used whenever possible.

These strategies will be implemented to ensure the quality and reliability of the data collected in the study.

### **Data collection instrument**

The clinical investigators will be responsible for collecting the information in RedCap (see Annex 5). RedCap provides a secure environment for the storage and management of clinical data, ensuring the privacy and confidentiality of the information. This transfer to RedCap will allow for better organization and access to the data, facilitating its analysis and subsequent use in the study.

